**Fig. 3 Fig3:**
[figure not shown]
Example of a happy face with teeth blurred using a Gaussian filter. (Model AF14, KDEF)

In order to avoid possible interference or habituation to the ABA emotional faces, we will use from a different face database for the ABM-T. Twelve pictures (half men, half women) will be selected from the FACES database created [87] at the Max Planck Institute for Human Development (MPIB). As in the ABA task, only two types of emotions will be used (12 happy and 12 sad) plus a set of 12 neutral expressions of the same actors/actress. All the faces will be also presented in a frontal view and the teeth of the happy faces will be also modified following the procedure described above. All pictures will be cropped and edited using Adobe Photoshop CS3. First, faces will be converted to a grey scale and all non-emotional features, such as surrounding parts, will be cropped [88]. All pictures will then be introduced into a grey square background (512 × 512 pixels). To blur the crop procedure, we will shade the outline of the faces into the background. The teeth of the happy pictures will be blurred by using a 10-pixel Gaussian filter. To avoid differences on energy or luminance all the pictures on both tasks, we will equate the contrast energy for assessment and training [86, 89]. Furthermore, a gamma correction will be applied to the 24” BENQ LCD monitor where the stimuli will be displayed. The presentations of the stimuli on the ABA task will be controlled through Tobii Studio software (2.0.6), whereas the stimuli presented during ABM-T will be controlled with an integration of Tobii Studio software (2.0.6) and E-Prime Studio software (2.0.8.22).

### Attentional Bias Assessment Task (ABA)

To assess participants’ attentional bias, we will administer a free viewing task comprising 108 trials [18]. Each trial will begin with a grey screen for 500 ms followed by a white cross fixation displayed at the center of the grey screen. Immediately thereafter, a random white number (1 to 3 and 7 to 9) will replace the cross for 500 ms. To ensure that participants maintain their attention on the fixation cross, we will follow Calvo & Avero's procedure [90] by which participants are asked to read the number out loud as quickly as possible. Afterwards, a pair of competing emotional faces (happy vs. sad; happy vs. neutral; sad vs. neutral) will be displayed for 3500 ms. Participants will be instructed to freely look at the faces, without any constraints, until the beginning of the next trial. Each emotional face will be presented equally often, and its position on the screen (right or left side) will be counterbalanced. In total, the task will be composed of 36 happy vs. sad, 36 happy vs. neutral and 36 sad vs. neutral trials that will appear in random order. The entire task will last about 12 min.

Dependent variables will comprise the latency to first fixation, the duration of first fixation, the number of fixations, and the total fixation time on each emotional face. Furthermore, attentional biases indices will be calculated based on these dependent variables, as done in previous research [18, 54].

### Attentional Bias Modification Training Task (ABM-T)

A wait- for- fixation paradigm will be used in the experimental group to train participants’ attentional patterns. In this paradigm, the progress of each trial depends on the maintenance of participants’ gaze to a previously determined target stimulus during a pre-specified length of time. In our paradigm, participants will be instructed to maintain their gaze on the most positive face of the pair (e.g., in the neutral vs. sad trials participants must hold their gaze at the neutral face; in the neutral vs. happy trials participants must hold their gaze at the happy face). Furthermore, to increase participants’ motivation in the task, especially challenging for depressed people [61], the cognitive demand of the task will increase. Whereas in the first set of trials, participants will have to hold their gaze on the target stimulus for 750 ms, in the second set they will have to do so for 1,500 ms to advance to the next trial. Within each block, participants will first perform the low demand condition (750 ms) before doing the high demand one (1500 ms).

The task will be composed of three independent blocks (happy vs. neutral; sad vs. neutral; and happy vs. sad). Each block, consisting of 96 trials, will be administered twice (i.e., one in each of the two training sessions). Both sessions will finish with the happy vs. sad block, as the others blocks will be counterbalanced across subjects. Thus, the entire task will consist on two independent sessions (two consecutive days) with 288 trials each (576 trials in total). Faces will appear equally often, and their position on the screen will be counterbalanced. Also, to reduce habituation and to foster adherence, we will randomly distribute the position of the faces along the horizontal or vertical axis of the screen.

In every block and condition, each trial will begin with a grey screen for 500 ms, followed by a white fixation cross appearing at the center of the screen until the participants fixate their gaze for 200 ms on it [13, 15]. After this initial required fixation, two faces will be simultaneously displayed on the screen until the required fixation on the target (i.e., 750 ms or 1,500 ms) is detected by the eye-tracker. As an immediate consequence of this fixation, a green square will be displayed on the face where the fixation has taken place (e.g., a neutral face in a neutral-sad trial; a happy face in a neutral-happy trial), thus providing immediate feedback to the participant. Each training session will last approximately 30 min (see Fig. 4).

**Fig. 4 Fig4:**
[figure not shown]
Attentional Bias Modification Training Task. Example of a happy-neutral condition trial. (Model 066, FACES)

### Control group in the attentional bias modification training task (yoked-control group)

For participants in the experimental group, the wait-for-fixation ABM-T paradigm will imply that each trial ends once the participant has spent a given amount of time looking at an area of interest (e.g., a happy face). Thus, in the experimental group, the duration of each trial is contingent upon the time each participant devotes to the target stimulus. An ideal control condition would be one in which participants in that condition would be exposed to the same amount of stimuli and the same total time of exposure.

To achieve this goal, we will use a yoked control group [91]. Participants in the experimental group will be the first ones to participate in the study, and we will measure the average total time they spend on each trial. Control participants will be exposed (“yoked”) to the same amount of time as participants in the experimental group, but they will not receive any type of explicit instruction or feedback. In carrying out this novel procedure in the context of ABM, we will ensure that participants in the experimental and control groups differ only in one way: the experimental group will experience a contingency between their gaze behavior and feedback, whereas the control group will not.

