**Methods:**

Based on sample size calculations, 32 dysphoric (BDI ≥13) participants will be allocated to either an active attentional bias training group or a yoked-control group. Attentional training will be individually administered on two sessions in two consecutive days at the lab. In the training task series of pairs of faces (i.e. neutral vs. sad; neutral vs. happy; happy vs. sad) will be displayed. Participants in the training group will be asked to localize as quickly as possible the most positive face of the pair (e.g., the neutral face in neutral vs. sad trials) and maintain their gaze on it for 750 ms or 1500 ms, in two different blocks, to advance to the next trial. Participants’ maintenance of gaze will be measured by an eye-tracking apparatus. Participants in the yoked-control group will be exposed to the same stimuli and the same average amount of time than the experimental participants but without any instruction to maintain their gaze or any feedback on their performance. Pre and post training measures will be obtained to assess cognitive and emotional changes after the training.

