### Participant recruitment and allocation

The sample size will be determined according to power calculations (G*Power; [65]) and based on Cristea et al.’s meta-analysis effect size (*g* = .33) [45]. A total of 32 dysphoric university students, with an estimated age range between 19 and 30 years, will voluntarily participate. All participants must have normal or corrected-to-normal vision via contact-lenses or glasses if required. Students who complete the two-session participation will receive course extra-points or/and a book as a reward for their participation. Participants will be selected based on their scores on Beck Depression Inventory-II - BDI-II [66]. A 13 points cut-off score will be used [67].

The study (see Fig. 2) is a controlled clinical trial with a placebo-control condition and will follow the Standard Protocol Items: Recommendations for Interventional Trials (SPIRIT) Statement for reporting trial protocols (see Additional file 1 for checklist).

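### Experimental participants are run before the controls, so on the likeliest reading group is aliased with testing period and the claim of a single difference between groups is not supported

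*Protocol article*

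**What the plan says.** The Protocol article fixes the running order in its section on the control group for the training task: "Participants in the experimental group will be the first ones to participate in the study". It continues that "we will measure the average total time they spend on each trial", and then that "Control participants will be exposed (“yoked”) to the same amount of time as participants in the experimental group". The Methods part of the abstract describes the control exposure as "the same average amount of time than the experimental participants".

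The same section draws a causal conclusion from this arrangement: "we will ensure that participants in the experimental and control groups differ only in one way", that one way being the link between gaze and feedback.

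On assignment, the abstract says only that "participants will be allocated to either an active attentional bias training group or a yoked-control group". Under Participant recruitment and allocation the study "is a controlled clinical trial with a placebo-control condition". The article uses the language of chance for stimuli and trial order in this study, not for assigning people.

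The Statistical analysis plan section tests Group × Time (with Trial type for the attention measures), and Group × Time around the anagram stress task. No term for period or enrolment order appears. Under Trial status, recruitment is described as ongoing.

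**The concern.** A yoked control is meant to equalise exposure so that only the training contingency differs. If one whole group is tested before the other, the groups also differ in when they were tested. Experimenter practice, point in the academic term and the kind of volunteer who comes forward early or late could all differ between the two periods. The article gives no recruitment calendar, so these are possible routes and not shown facts.

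Every between-group conclusion rests on a Group × Time contrast. If change over two consecutive days differs between the periods, the contrast picks that difference up as a training effect. The stress task is more exposed still. The Study design overview places it only in session 2, after training, so there is no pre-training measure of stress reactivity against which a cohort difference could be netted out.

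**Working it through.** The plan gives no figure on this point, so there is none to reproduce.

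**Inputs.** Total N = 32 and g = 0.33 (Participant recruitment and allocation); α = 0.05 (Statistical analysis plan). The allocation ratio is not stated, so 16 per group is assumed. The size of any period difference is also assumed and is varied below.

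**Step 1: does the text imply strict sequence?** A group's average time per trial is known only once that group has been run. The statement that experimental participants go first, the reference to their average total time, and the abstract's wording on average time all point the same way. Pair-by-pair yoking with interleaved enrolment does not fit these sentences well.

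**Step 2: can period be separated from group?** If all experimental participants come first, a two-level period indicator equals one minus the group indicator. The design matrix with columns for intercept, group and period then has rank 2, not 3, so the period effect is not estimable alongside group. A linear enrolment-order term is estimable: its correlation with group is 0.87 in absolute value, giving a variance inflation factor of 1/(1 − 0.866²) = 4.0 and a standard error about √4.0 = 2 times as large. With no overlap in time between the groups, that adjustment is extrapolation and cannot capture an abrupt change.

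**Step 3: what would a period difference do to the test?** In a 2 × 2 mixed design, the Group × Time F test is the square of the two-sample t test on change scores. With no training effect and a period difference of d SDs of the change score, the noncentrality is d/√(2/16) = 2.83 d on 30 degrees of freedom. The two-sided 5% rejection rates are:

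| Assumed d | Noncentrality | Rejection rate |
|---|---|---|
| 0 | 0 | 5.0% |
| 0.20 | 0.57 | 8.5% |
| 0.33 | 0.93 | 14.8% |
| 0.50 | 1.41 | 27.8% |
| 0.80 | 2.26 | 59.1% |

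The 0.33 row has the same numerical size as the effect on which the plan bases its sample size.

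**Step 4: what cancels?** A stable difference in level between the two cohorts is present before and after training and drops out of Group × Time. A difference in change does not. Nor does a difference in reactivity to the stress task, because the pre-task to post-task change is itself the outcome there.

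**The case against.** The strongest reply is that this is a condensed article. The flow diagram and the SPIRIT checklist are not at hand, and the method of randomisation may be set out in the full protocol. A pool screened on the BDI-II could have been randomised first and then scheduled by group. This stands against one tempting inference: a reader might conclude that allocation is non-random and always known to whoever recruits. The article does not say so, and its silence does not establish it. What it fixes is the order of participation. The reply does not rescue the comparison, because a pool randomised and then tested group by group still has group aliased with testing period.

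Second, yoking is classically done pair by pair, and the Background describes the control exposure simply as the same amount of time. Strict sequence is therefore the likeliest reading and not a certainty.

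Third, no passage supports a drift of any given size. Two sessions of about 80 minutes for 32 people come to 32 × 2 × 80 = 5,120 minutes, about 85 laboratory hours or 43 per group, so both phases could fall within one term. This stands: the rejection rates are conditional illustrations.

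Fourth, a reader might infer that no adjustment could help. That is slightly too strong, since a smooth trend is estimable and baseline measures can address measured cohort differences. Neither removes an abrupt or unmeasured period effect. A reader might also look for harm in comparisons of post-training values alone, but the article plans none.

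**Conclusion.** The point holds as a matter of design. The stated running order, read with yoking to the group average, makes group and testing period indistinguishable on the likeliest reading. The claim that the groups differ in one way only is contradicted by the plan's own order of testing. Unless participants were randomised before scheduling, a step the article does not describe, allocation could also be predicted from the date.

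The size of any bias is unknown. Assuming 16 per group, no training effect and a period difference in change of 0.33 or 0.50 SD, the nominal 5% test would reject about 15% or 28% of the time. The documents do not show that such a difference exists.

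**What to change.** Replace the sentence that puts the experimental group first. Run a short lead-in of experimental participants whose timings, as individual records or as a running average, set control exposure. Then allocate all remaining participants concurrently by a concealed random sequence in small blocks. Keep all 32 in the main analysis and add the concurrently allocated participants as a sensitivity set.

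The cost is a randomisation list and a change to the stimulus script so that it reads stored timings. There are three downsides. Early controls rest on few timing records. Exposure matching departs slightly from the full-group average now planned. The sensitivity set is smaller than 32: a lead-in of k leaves 32 − k, and 1:1 allocation of those gives 16 + k/2 experimental and 16 − k/2 control participants overall, so the block ratio must be adjusted if equal groups are wanted. Taking the lead-in timings from pilot volunteers would avoid this but needs extra people.

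Recruitment is described as ongoing, so the change may still be possible for those not yet run. If the experimental group is already complete, describe the comparison as non-concurrent and withdraw the statement that the groups differ in only one way.

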**Discussion:**

The findings from this research will provide a proof-of-principle of the efficacy of eye-tracking paradigms to modify attentional biases and, consequently, to improve depressed mood. If the findings are positive, this new training approach may result in the improvement of cognitive bias modification procedures in depression.

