### The proposal of a new ABM intervention

Taken together, these conceptual and methodological considerations point towards modifications in current ABM procedures [61]. The aim of this study will be to apply eye-tracking methods to modify specific components of attentional bias in depression. Eye-tracking technology enables us to train attention by following strict performance and time-based criteria as well as to specify the components of attention (i.e., disengagement from negative information, engagement and maintenance in positive information) to be targeted in the training, critical to providing a theory-driven intervention [59]. The proposed ABM procedure accomplishes this by providing individualized trial-by-trial feedback on trainees’ gaze allocation during the attentional processing of different emotional stimuli. This new procedure should maximize awareness of attention allocation to increase regulatory control in redirecting attention in an adaptive manner [15, 62].

The inclusion of individualized feedback on trainees’ performance during the attention training [57], in combination with explicit guidance of attention in the intended direction [15], may be a promising approach. Explicitly instructing participants to redirect attention from negative to positive information and providing them with online feedback on their performance can increase top-down regulation of attention and diminish emotional reactions to stressors [15]. Therefore, in the current trial, we aimed to develop a novel ABM method for treating depression-related attention biases, relying not only on the use of eye-tracking contingencies, but also on online feedback and explicit implementation of top-down regulation to train attention patterns. Furthermore, a significant improvement of our proposed experimental design over previous studies is related to the control group. In our study we will design a ‘yoked-control’ condition where participants in the control group will be exposed to the same experimental stimuli the same amount of time than participants on experimental condition, but without receiving any type of training or contingency for those stimuli.

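### The yoked control does not isolate the gaze–feedback contingency: the trained group also gets an explicit instruction, so the contrast is whole package versus passive exposure

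*Protocol article*

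**What the plan says.** The section on the yoked-control group describes the control condition and then says what it achieves. Controls see the stimuli for the same time as the experimental group, but "they will not receive any type of explicit instruction or feedback". The next sentence claims that "participants in the experimental and control groups differ only in one way", and specifies the difference: "the experimental group will experience a contingency between their gaze behavior and feedback, whereas the control group will not". The abstract's Methods paragraph describes controls in the same terms, as viewing "without any instruction to maintain their gaze or any feedback on their performance".

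The section on the training task (ABM-T) sets out what the experimental group gets. First, "participants will be instructed to maintain their gaze on the most positive face of the pair". Then each trial continues until the required fixation is detected, whereupon "a green square will be displayed on the face where the fixation has taken place".

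The background section on the new ABM intervention describes the method as resting on eye-tracking contingencies and, in addition, on online feedback and explicit top-down regulation. It gives a reason for the combination: "Explicitly instructing participants to redirect attention from negative to positive information and providing them with online feedback on their performance can increase top-down regulation". The abstract's Discussion says that the findings will give a "proof-of-principle of the efficacy of eye-tracking paradigms to modify attentional biases".

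**The concern.** Two consecutive sentences in the yoked-control section do not agree. The first withholds instruction from controls. The second says that only the gaze–feedback contingency separates the arms. The instruction is not part of that contingency: a person can be told where to look without gaze-dependent feedback, and gaze-dependent feedback can be given without telling the person the goal.

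At stake is what a positive result would mean. A reader who accepts the single-difference claim would credit any between-group effect to the contingency, which is the novel technical feature. If telling people to look at the more positive face produces some or all of the effect, that credit is misplaced. The article also counts the control group as a notable advance on earlier studies, so the claim carries weight in its argument.

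**Working it through.** No figure in the plan needs reproducing. The check sets the arms side by side and asks what the planned contrast identifies.

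**Step 1. Components by arm** (abstract Methods; ABM-T section; yoked-control section)

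| Component | Experimental | Control |
|---|---|---|
| Same stimuli | yes | yes |
| Average exposure time | sets it | matched to it |
| Instruction to hold gaze on the more positive face | yes | no |
| Green-square feedback | yes | no |
| Trial end depends on gaze | yes | no |

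The last two rows largely deliver the contingency that the article names. The instruction row is not covered by it.

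**Step 2. What the analysis can identify.** The statistical analysis plan section uses one Group factor with two levels throughout, so each outcome yields one between-group difference in pre–post change. Write *I* for the contribution of the instruction, *K* for that of the gaze–feedback contingency (square and gaze-dependent trial end together), and *IK* for any interaction. Then

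change(experimental) − change(control) = *I* + *K* + *IK*.

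This is one equation with at least two unknowns. If the observed difference is *D*, then (*I*, *K*) = (*D*, 0), (0, *D*) and every split between them fit equally well. As a design matrix with columns for intercept, instruction and contingency, the rows are (1, 1, 1) for experimental and (1, 0, 0) for control, so the rank is 2 with 3 columns. Counting the feedback signal separately from the gaze-dependent trial end gives rank 2 with 4 columns. More participants repeat the same two rows and leave the rank at 2.

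**Step 3. A concrete rival explanation for the attentional outcome.**
- Dose of instruction: 3 blocks × 96 trials = 288 per session, and 288 × 2 sessions = 576 trials under the instruction in the experimental arm, against 0 in the control arm.
- Timing: the study design overview places the second training session immediately before the post-training attentional assessment (ABA).
- Similarity: the ABA is free viewing of the same three kinds of pair used in training (happy–sad, happy–neutral, sad–neutral), and its outcomes are fixation measures on the emotional faces.

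Participants who have just spent a session looking for the more positive face on request may go on doing so when left to look freely. That would produce a Group × Time effect on the ABA even if the contingency contributed nothing.

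**The case against.** The strongest reply is that the trial tests a package and largely says so. The background section names contingency, feedback and explicit guidance together as the intervention. The ABM-T section includes the instruction in its account of the paradigm, so the abstract's phrase about eye-tracking paradigms can be read as the whole package. The closing discussion gives the yoked group the narrower task of controlling exposure time. On this view one sentence is too strong and the rest is sound. Much of this stands: package versus exposure-matched viewing is a legitimate comparison, and aliased components are normal in any two-arm trial of a multi-component treatment. What does not stand is the sentence itself, which claims a property that the design lacks.

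Four stronger readings are tempting, and the documents do not support them.

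- *That there are three separate unacknowledged differences.* The green square and the gaze-dependent trial end are mostly how the named contingency is delivered. The clear unacknowledged difference is the instruction.
- *That the article itself says instruction alone works.* The background sentence credits instruction and online feedback jointly. It supports treating explicit guidance as a distinct ingredient, not as sufficient by itself.
- *That the whole between-group difference would be an instruction effect.* Nothing shows this. The ABA uses a different face set, and participants are told there to look freely. These features weaken simple carry-over without excluding it. Carry-over of a gaze instruction also does not readily explain effects on questionnaires, the scrambled sentences task or the anagram stress task.
- *That the control condition must be changed.* Giving controls the same instruction and a green square could itself train them, and it would change the comparator while the trial is recruiting.

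**Conclusion.** The single-difference claim is wrong as written, on the instruction alone. The Group contrast estimates the combined effect of instruction, feedback and gaze contingency against passive viewing matched on stimuli and average exposure time. The share due to the contingency is not identified at any sample size. The limit applies to every outcome. The specific rival explanation, instruction carry-over, bears mainly on the ABA.

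This rests on the article's own description of the two arms, and on there being no third arm or matching instruction for controls elsewhere; the article mentions neither. It does not call the comparison invalid, and it requires no change to the outcomes, the ANOVAs or the sample size. It takes the groups as otherwise comparable. The yoked-control section also has the experimental participants go first, but that is a separate matter and is not used here.

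**What to change.** Two wording changes.

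1. In the yoked-control section, replace the single-difference sentence with one to this effect: *The yoked control matches the experimental group on stimuli and average exposure time only. The experimental group additionally receives an explicit gaze instruction, feedback, and trial progress that depends on gaze. The comparison therefore estimates the effect of this package against passive exposure.*
2. State, next to the proof-of-principle sentence in the abstract and in the main discussion, that conclusions refer to the whole package and not to the eye-tracking contingency by itself. Add that carry-over of the instruction is a possible explanation for a change on the ABA.

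The cost is a few sentences of text. Trial conduct, the control condition, the data collected and the planned analyses stay as they are, so the change can be made while recruitment continues. What the sponsor gives up is a claim about the contingency alone, which the design cannot support.
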